# Chinese herbal medicine (Ma Zi Ren Wan) for functional constipation: study protocol for a prospective, double-blinded, double-dummy, randomized controlled trial

**DOI:** 10.1186/1745-6215-14-366

**Published:** 2013-11-04

**Keywords:** Functional constipation, Chinese herbal medicine, Ma Zi Ren Wan, Randomized controlled trial

## Abstract

**Background:**

Functional constipation is a common clinical complaint. Although the effectiveness of Ma Zi Ren Wan for alleviating functional constipation symptoms has been proven in a previous randomized placebo-controlled study, further evidence is needed to make clinical recommendations about Chinese herbal medicine. In particular, a comparison with conventional western medicine for functional constipation patients is needed.

**Methods/Design:**

This is a prospective, double-blinded, double dummy, randomized, controlled trial. After a 2-week run-in period, eligible patients (Rome III) with excessive traditional Chinese medicine syndrome will randomly be assigned to the Chinese medicine arm (Ma Zi Ren Wan and western medicine placebo), western medicine arm (senna and Chinese medicine placebo) or placebo arm (Chinese medicine placebo and western medicine placebo). Patients will undergo an 8-week treatment and an 8-week follow-up. The primary outcome is the responder rate for complete spontaneous bowel movement (CSBM) during treatment. Patients with a mean increase of CSBM ≧1/week in comparison with their baselines are defined as responders. The secondary outcomes include responder rate during follow-up, changes of colonic transit as measured with radio-opaque markers, individual and global symptom assessments, and reported adverse effects.

**Discussion:**

This study is the first study to compare a Chinese Herbal Medicine (Ma Zi Ren Wan) with a laxative that is commonly used in the clinical practice of western medicine, and with a placebo. This study will complete the investigation of Ma Zi Ren Wan for functional constipation, and should, therefore, suggest recommendations for clinical practice. Furthermore, the process of first conducting a systematic review, then implementing a dose determination study followed by a placebo-control trial, and finally, comparing traditional Chinese medicine with an active conventional medicine in a controlled trial can be a reference to other researches on Chinese medicine interventions in the future.

**Trial registration:**

NCT01695850

## Background

Constipation affects a substantial portion of the population, involving an estimated 12% to 19% of Americans [1], 14% of Asians [2], and up to 27% of the global population, depending on demographic factors, sampling, and definition [3]. Treatments for constipation usually include fiber supplements, osmotic and stimulant laxatives, stool softeners, and sometimes enemas for refractory constipation [4]. With the unsatisfactory response to current symptomatic treatments [5], many patients seek help from traditional Chinese medicine (TCM), mostly by taking Chinese herbal medicine (CHM) [4].

According to TCM theory, constipation can be divided into excessive and deficient patterns based on the underlying etiology [6-8]. The former is characterized by the presence of Heat or pathological accumulation of Qi (Qi stagnation), while the latter is characterized by the deficiency of Qi, Ying or Yang. The patent formula Ma Zi Ren Wan (MZRW) was first recorded in the TCM classic, 'Discussion of Cold-induced Disorders’ (ShangHanLun) [6], and this formula has been commonly used for excessive constipation in China and other Asian countries for more than two thousand years since the Han Dynasty (A.D. 200). It comprises six herbs: *Semen Cannabis Sativae*, *Semen Pruni Armeniacae*, *Radix Paeoniae*, *Fructus Immaturus Citri Aurantii*, *Cortex Magnoliae* and *Radix et Rhizoma Rhei*. Through the combined action of these herbs, MZRW can moisten the intestines, drain Heat, promote the movement of Qi and unblock the bowel [9]. Based on modern pharmaceutical studies, MZRW can stimulate intestinal mucosa, increase secretion, accelerate intestinal peristalsis and decrease water absorption [10,11].

Our research team began studying MZRW for functional constipation (FC) in 2006. We found that available studies had significant methodological flaws and lacked replicable validation; thus, clinical findings could not be definitively determined [12]. Therefore, the efficacy and safety of MZRW had to be justified by first determining the optimal dose. The currently recommended dose (5.0 g b.i.d.) was compared with higher (7.5 g b.i.d.) and lower doses (2.5 g b.i.d.); the study was supported by the WooFo Medical Foundation. The dose of 7.5 g b.i.d. was found to have better therapeutic effect than that of 2.5 and 5.0 g b.i.d. among 96 subjects (32 per arm). Second, MZRW in optimal dosage (7.5 g b.i.d.) was compared with a placebo for FC patients with excessive TCM Syndrome in a randomized, double-blind clinical trial, which was supported by the Health and Health Services Research Fund. In this study, 120 subjects were randomized into two arms (60 per arm). Response rates for the MZRW and placebo groups were 43.3% and 8.3% during treatment, and 30.0% and 15.0% in the follow-up period, respectively (*P* <0.05). Those in the MZRW group showed benefits in terms of increased bowel movement, relief in the severity of constipation and straining, and effective reduction in the use of rescue therapy when compared with placebo. These encouraging results suggested that the higher dose, which had not been the recommended dosage in the Clinical Handbook of Chinese Herbal Formulae [13], was in fact safe and effective for alleviating FC when compared with the placebo [14].

In the current trial, we seek to evaluate the efficacy and safety of MZRW by comparing it with the commonly used stimulant laxative senna, as well as with a placebo, for patients with FC diagnosed with the TCM excessive syndrome. Senna is a stimulant laxative which facilitates the passage of stools by altering intestinal electrolyte transport and increasing intestinal motor activity [15]. Although no placebo-controlled trials were found, laxatives containing senna and fiber were more efficacious than lactulose [4]. Up to 26% of the patients underwent successful relief of impaction with senna combined with mineral oil [16]. Due to its low cost, safety and ease of ingestion, senna is widely adopted and prescribed in clinical practice. The use of senna remains the first-line treatment for the management of constipation according to the local guidelines of internal medicine published by the Hospital Authority, Hong Kong [17].

The study was financially supported by Food and Health Bureau, Hong Kong, China, through its Health and Health Services Research Fund (project no. 09101501) and was registered with an identifier (NCT01695850) in Clinical Trial.gov. This funding source had no role in the design of this study and will not have any responsibility during its execution, analyses, interpretation of the data, or decision to submit results.

## Materials and methods

### Study design

This is a double-blinded, double-dummy, and placebo-controlled trial with three parallel groups. The protocol design was based on the recommendations made in the 'Design of Treatment Trial for Functional Gastrointestinal Disorders’, as proposed by the Rome III Working Team [3] and the Consolidated Standards of Reporting Trials (CONSORT) statement [18]. Two hundred and ninety-one participants were recruited from Lee Kee Memorial Dispensary (General outpatient clinic), Li Ka Shing Specialist Clinic of Prince of Wales Hospital and clinics of the School of Chinese Medicine, Hong Kong Baptist University. After a 2-week run-in period, eligible subjects were randomly assigned to one of three arms, the Chinese medicine (CHM) arm, the western medicine (WM) arm, and the placebo arm. The CHM arm received MZRW and WM placebo, the WM arm received senna and the CHM placebo, and the placebo arm received the CHM placebo and the WM placebo. All three groups then underwent an 8-week treatment and an 8-week follow-up period. Five visits in total were scheduled for each subject: one visit each in week 0, week 2, week 4, week 8 and week 16. The participant flowchart is listed in Figure 1 and the participant timeline is listed in Figure 2. The study protocol was approved by the Hong Kong Baptist University Ethics Committee on the Use of Human Subjects for Teaching and Research (Approval no. HASC/10-11/16) and the Joint Chinese University of Hong Kong-New Territories East Cluster Clinical Research Ethics Committee (Approval no. CRE-2013.192-T).

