### Interventions

*CHM intervention*: As reported previously, MZRW is composed of *Fructus Cannabis* (HuoMaRen), *Radix et Rhizoma Rhei* (DaHuang), *Radix Paeoniae Alba* (BaiShao), *Semen Armeniacae Amarum* (KuXingRen), *Fructus Aurantii Immaturus* (ZhiShi) and *Cortex Magnoliae Officinalis* (HouPo) [10]. The composition and action of each herb are summarized in Table 1[17]. The placebo was made from dextrin (76.03%), tea essence (23.61%), gardeniaflavin (0.02%) and *caramel (0.34%) to achieve color, smell, taste and texture comparable to MZRW granules. Patients were instructed to dissolve a sachet of granules (7.5 g) in 150 ml of hot water; and to* take the solution orally twice daily for 8 weeks. Quality control of the crude herbs authentication report is listed in Additional file 1.

**Table 1 T1:** Composition and action of Ma Zi Ren Wan (MZRW)

**Ingredients**	**%**	**g/****sachet**	**g/****day**	**Action**
*Fructus Cannabis*	35.7	10.8^a^	21.7	TCM: Moistening the bowel and relieving constipation
				Pharmaceutical study: 1. Purgative effect, 2. Hypotensive effect
*Radix et Rhizoma Rhei*	17.9	5.4	10.9	TCM: Draining heat and relieving constipation
				Pharmaceutical study: 1. Purgative effect, 2. Antimicrobial effect, 3. Antineoplastic and ant mutagenic effect, 4. Hemostatic effect, 5. Immunosuppressive effect, 6. Choleretic effect
*Semen Armeniacae Amarum*	17.9	5.4	10.9	TCM: Reliving constipation by guiding Qi downward
				Pharmaceutical study: 1. Laxative effect, 2. Antitussive and antiasthmatic effect, 3. Analgesic effect, 4. Antineoplastic and antimutagenic effect
*Radix Paeoniae Albo*	8.9	2.7	5.4	TCM: Nourishing Yin and retaining homeostasis
				Pharmaceutical study: 1. Analgesic effect, 2. Antimicrobial and anti-inflammatory effect, 3. Immunologic effect
*Cortex Magnoliae Officinalis*	10.7	3.3	6.5	TCM: Promoting circulation of Qi and relieving flatulence
				Pharmaceutical study: 1. Central muscle-relaxation effect, 2. Anti-emetic effect, 3. Anti-ulcerative effect 4. Central inhibitory effect, 5. Antimicrobial effect
*Fructus Aurantll Immaturus*	8.9	2.7	5.4	TCM: Promoting circulation of Qi and relieving flatulence
				Pharmaceutical study: 1. Diuretic effect, 2. Two-way effect on gastrointestinal smooth muscle, 3. Cardiovascular stimulating effect

*TCM*, traditional Chinese medicine.

^a^Each gram of *MZRW* granule is equivalent to 4.05 g of raw herbs.

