### Outcomes

Participants recorded stool frequency, stool form (on the 7-point Bristol stool scale, ranging from 'Separate hard lumps’ to 'Watery’), and feeling of complete evacuation (yes/no). They were also required to log intake of research medication, rescue drug and/or any other medication use throughout the study in a daily diary. Principal investigators (PIs) and research assistants (RAs) interviewed patients at the end of Week 2 (baseline), Week 4 (within treatment), Week 8 (end of treatment), and Week 16 (end of follow-up), for symptoms, compliance, and occurrence of adverse events. Data on global symptom improvement, individual bowel symptoms and stool consistency were collected.

Individual assessment of constipation and related symptoms (severity of constipation, sensation of straining, incomplete evacuation, bloating, abdominal pain/cramping, nausea and passing of gas) were recorded using a 7-point ordinal scale (0 = not at all, 6 = very severe) [see Additional file 2: Table S1] on a designated form that participants filled out during every visit [3]. Global symptom improvement was defined as the participant's subjective feeling of adequate relief of symptoms. For this purpose, participants were asked to rate their impression of changes in constipation by scoring (in comparison with their baseline (Week 2) scores) their impression of these changes from 0 to 6 to represent that they were feeling markedly worse or better at the respective extremes [3]. The response categories are collapsed to simply 'Improved’ for score 4 to 6, 'Same’ for score 3 or 'Worse’ for score 0 to 2 [24].

The primary outcome will be the response rate for CSBM during the treatment period: a clinically meaningful endpoint that combines an objective measure (number of bowel movement) with a subjective measure (feelings of patients as to completeness of defecation) [25,26]. Participants with a mean increase of CSBM ≧1/week compared with the last 14 days of the run-in period are defined as responders.

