### Statistical analysis

All efficacy and safety analyses will be conducted according to the intention-to-treat (ITT) principle. Missing values will be imputed by the last-observation-carried-forward method. The statistical analysis will be performed using the Statistical Packages of Social Sciences (SPSS) for Windows version 16.0. The statistical significance is defined as two-sided *P* value of <0.05. Baseline characteristics will be reported as mean (SD). Baseline differences among the groups will be assessed with the use of Student’s t-test for normally distributed continuous variables and the non-parametric Mann-Whitney U test for non-normally distributed variables. For categorical variables, chi-squared test or Fisher’s exact test will be used. Comparisons between groups will be conducted by using an analysis of covariance (ANCOVA) with baseline as covariate. All items and subscales will be compared between groups for each 6-week treatment using ANCOVA, with treatment group as a factor in the model and baseline as the covariate. The changes from baseline to endpoint of treatment in scores will be tested with repeated measure analysis of variance (ANOVA). Within group differences will be assessed with paired t-test for normally distributed data and Wilcoxon signed-rank test for non-normally distributed data.

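### The symptom ANCOVA is tied to a 6-week treatment in a trial that treats for 8 weeks, and the printed visit weeks share no single time origin

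*Protocol article*

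**What the plan says.** **Treatment length.** The abstract states: "Patients will undergo an 8-week treatment and an 8-week follow-up". Study design repeats it after describing the 2-week run-in: "All three groups then underwent an 8-week treatment and an 8-week follow-up period". Interventions instructs patients on granules to "take the solution orally twice daily for 8 weeks" and gives the same duration for the tablets. The section on data collection and dropout puts the whole trial at 18 weeks, with 8 weeks on medication and five visits.

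**Visits.** Study design schedules "one visit each in week 0, week 2, week 4, week 8 and week 16". Outcomes assigns meanings to four of these: "Week 2 (baseline), Week 4 (within treatment), Week 8 (end of treatment), and Week 16 (end of follow-up". The same section scores global improvement "in comparison with their baseline (Week 2) scores".

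**Analysis.** Statistical analysis states: "All items and subscales will be compared between groups for each 6-week treatment using ANCOVA", with treatment group as factor and baseline as covariate. The next sentence reads: "The changes from baseline to endpoint of treatment in scores will be tested with repeated measure analysis of variance (ANOVA".

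**The concern.** There are two conflicts, both in operative text rather than background.

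First, the ANCOVA sentence names a treatment period that the article defines nowhere. It is two weeks shorter than the one patients actually receive.

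Second, the visit numbers cannot all be counted from the same day. If Week 2 is baseline at the end of run-in, then Week 8 comes too early to close 8 weeks of treatment. If Week 8 closes 8 weeks of treatment, then Week 2 cannot be baseline on that same clock.

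The two conflicts also seem to support each other, because Week 2 to Week 8 is exactly 6 weeks. Someone following the text literally could therefore place the end-of-treatment assessment at treatment week 6, or cut a diary-based secondary comparison two weeks short.

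**Working it through.** **Inputs.** Run-in 2 weeks, treatment 8 weeks, follow-up 8 weeks, and visit weeks 0, 2, 4, 8 and 16 (Study design). Visit labels (Outcomes). Total 18 weeks (data collection section). ANCOVA period 6 weeks (Statistical analysis). Two tablets nightly and 56 tablets per bottle; two sachets daily and 28 sachets per bag (Interventions).

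**1. The plan's own total.** 2 + 8 + 8 = 18 weeks. The stated duration reproduces from the period lengths.

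**2. The printed visits.** Intervals: (2 - 0) + (4 - 2) + (8 - 4) + (16 - 8) = 2 + 2 + 4 + 8 = 16 weeks. That is 18 - 16 = 2 weeks short.

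**3. Each possible origin.**

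| Week 0 is | Treatment | Follow-up | Total | Conflict |
|---|---|---|---|---|
| Start of run-in | 8 - 2 = 6 | 16 - 8 = 8 | 16 | Treatment and total each 2 weeks short |
| First dose | 8 - 0 = 8 | 16 - 8 = 8 | 2 + 16 = 18 | Week 2 falls on treatment, so it cannot be baseline; the run-in visit would be week -2 |
| Run-in for weeks 0 and 2, first dose for weeks 4, 8 and 16 | 8 | 8 | 18 | None in timing; two of the five labels use a different clock from the other three |

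On the third reading the visits fall at 0, 2, 2 + 4 = 6, 2 + 8 = 10 and 2 + 16 = 18 weeks from the start of run-in. The intervals are 2 + 4 + 4 + 8 = 18. Subtracting 2 gives -2, 0, 4, 8 and 16 from first dose. None of the five visits is then mistimed.

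**4. The Week 4 visit.** If Week 4 were instead on the run-in clock, the visits would be 0, 2, 4, 10 and 18, with intervals 2 + 2 + 6 + 8 = 18. The total is again right, so the arithmetic cannot say whether this visit is 2 or 4 weeks after first dose. One bottle lasts 56 / 2 = 28 days, which favours 4 weeks, but that is an inference from packaging.

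**5. The 6-week period.** 8 - 6 = 2 weeks shorter than treatment. It equals Week 8 minus Week 2 read literally on the run-in clock (8 - 2 = 6). Supply check: 8 weeks needs 2 × 56 = 112 tablets (2 bottles) and 112 sachets (4 bags); 6 weeks needs 2 × 42 = 84 tablets (1.5 bottles) and 84 sachets (3 bags). The bottles fit 8 weeks; the bags fit either. This adds little, since 8 weeks is stated directly and repeatedly.

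**6. Which scores the two analyses would use.** Outcomes says the symptom form is completed at visits.
- With the clock restarting at first dose, the scores lie at treatment weeks 0, 4 and 8, then at week 16. There is no week-6 score to analyse.
- Read literally on the run-in clock, the visit 6 weeks after baseline is the one labelled end of treatment.

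On either reading, the ANCOVA and the repeated-measures ANOVA draw their end-of-treatment symptom scores from the same visit.

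**The case against.** The strongest reply is that the intended design is plain. Run-in, treatment and follow-up lengths are each stated, they add to the stated total, and Study design sends the reader to Figure 2 for the timeline. That figure is not shown and may give the origin. This stands to the extent that a restart at first dose cannot be called undeclared. It does not make the ANCOVA sentence agree with the dosing statements, nor does it put the visit weeks in the text on one clock.

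A second reply is that 6 weeks is not a stray number, because it matches the printed calendar counted from run-in. That is correct, so it would be too strong to call it wrong on every reading. What it contradicts is the stated 8-week treatment.

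A reader might also infer two harms that the text does not support:
- **That the ANCOVA and the repeated-measures ANOVA would test symptom scores at different times.** Step 6 shows that they would not.
- **That Week 2 might be taken for an on-treatment baseline.** Outcomes names it as baseline twice, and Study design puts randomisation after the run-in, so which visit is meant is clear even though its number is not on the first-dose clock.

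Finally, this is not a complaint about detail left to a fuller protocol or an analysis plan. The conflicting statements are all printed in the article.

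**Conclusion.** The point holds as a minor correction. The ANCOVA sentence understates the treatment period by 2 weeks (6 against 8). The visit numbers fit no single origin, and read from run-in they lose 2 weeks of treatment and of total duration (6 against 8, and 16 against 18).

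The most consistent reading, a restart at first dose, leaves 0 of 5 visits mistimed. That reading is inferred, and so is the placing of the Week 4 visit at treatment week 4.

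The consequence is limited to the visit labels and the secondary comparisons, chiefly any diary-based item that someone might summarise over 6 weeks instead of 8. A reader might extend it to the primary outcome, but that is defined over the treatment period against the last 14 days of run-in, and depends neither on visit numbers nor on the ANCOVA sentence. The sample size rests on response rates, significance level, power and dropout, with no time input. Neither is affected.

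**What to change.** 1. In Statistical analysis, change the ANCOVA period from 6 to 8 weeks.
2. In Study design and Outcomes, state one origin. Counting from first dose: run-in visit at week -2, baseline at week 0, mid-treatment visit at week 4, end of treatment at week 8, end of follow-up at week 16. The equivalent from the start of run-in is 0, 2, 6, 10 and 18. The reference to a Week 2 baseline for global improvement should be renumbered to match.
3. The sponsor should confirm that the mid-treatment visit is 4 weeks after first dose. If it is 2 weeks after, its label becomes week 2 from first dose (week 4 from the start of run-in) and the other labels are unchanged. Figure 2 should be checked against the same numbering.

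The cost is a few words in three sections, with no added visits or patients. According to Trial status, 20 subjects had been enrolled at submission and none had completed treatment, so at that point the clarification could still precede any end-of-treatment assessment.

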**Figure 1 F1:**
[figure not shown]
Participant flowchart.

**Figure 2 F2:**
[figure not shown]
**Schedule of enrolment, ****intervention and assessments.**

### Participants

*Setting*: The study was performed at Lee Kee Memorial Dispensary (general outpatient clinic), Li Ka Shing Specialist Clinic of Prince of Wales Hospital and Clinics of the School of Chinese Medicine, and Hong Kong Baptist University. The participants were enrolled from the public through advertisements in local newspaper and out-patient clinics.

*Diagnostic criteria for FC* (*Rome III*) [3]: 1) At least two of the following occurrences more than 25% of the time were required for a diagnosis of functional constipation: straining, lumpy or hard stools, sensation of incomplete evacuation, sensation of anorectal obstruction/blockage, manual maneuvers to facilitate, or fewer than three defecations per week; as well as 2) the rare presence of loose stools without the use of laxatives; and also 3) insufficient criteria for a diagnosis of irritable bowel syndrome.

*Diagnostic criteria for excessive constipation in TCM theory*[6]: Any three of the chief symptom manifestations of Heat and/or Qi stagnation were required for a diagnosis of functional constipation: 1) dry, hard stools; 2) difficult bowel movements; 3) abdominal distension, with or without tenderness; 4) belching; 5) dry mouth or halitosis; 6) red tongue with dry and/or yellow coating; and 7) Wiry pulse.

*Inclusion Criteria*: Patients were included if they had all of the following: 1) met the diagnostic criteria for FC (Rome III); 2) met the diagnostic criteria for excessive constipation in TCM theory; 3) were age 18 to 65 years (inclusive); 4) had a complete spontaneous bowel movement (CSBM) ≦2 times/week (CSBM is defined by feeling of complete passage of stool after defecation, rather than partial or incomplete evacuation, without the use of any laxative or enema within 24 hours) [19]; 5) exhibited severity of constipation ≧3 points (on a 7-point scale) [20]; 6) had a total symptom score ≧8 points (on a 7-point scale for constipation-related symptoms); 7) had a normal colonic examination (barium enema or colonoscopy) within five years; and 8) had a normal liver and renal function in blood test within 3 months.

*Exclusion criteria*: Patients were excluded if they had one or more of the following: 1) drug-induced constipation; 2) secondary causes of constipation (that is, medical history of diabetes mellitus, unstable thyroid disease); 3) abdominal surgery within one year (that is, Caesarean operation); 4) severe diseases (that is, cancer, acute asthma); 5) allergy to CHM (that is, G6PD deficiency); 6) pregnancy or breast-feeding; or 7) psychiatric or addictive disorders requiring medications with side effects of constipation.

